### Economic analysis

If information meetings with small groups of physicians (*Emilia-Romagna and Friuli Venezia Giulia study*) or with single physicians (*Sardinia study*) will be more effective than no meetings, we will conduct economic evaluations for each study to evaluate the opportunity cost of our interventions.

We will adopt the perspective of the National Health Service, not considering indirect costs [18]. As we expect no health consequences of the changes in prescribing patterns, we will conduct a cost-minimisation analysis evaluating whether the savings on drug-costs are greater than the costs of the intervention.

*In the Emilia-Romagna and Friuli Venezia Giulia study we will consider *the cost of the evidence based bulletins specifically developed. In the *Sardinia study we will consider both *the cost of the evidence based bulletins specifically developed and the cost of the translation of the articles used as "traditional" information material.

All costs will be reported in monetary as well as natural units. An overview of all included costs and data sources is presented in Table 1. As all costs occur within the same year, we will not apply discounting.

**Table 1 T1:** Input variables in the economic analysis

**Variable**	**Data-source (natural units)**	**Source for monetary units**
Cost for development of evidence based material and translation of drug bulletin	Time spent	Salary payments
Training of outreach pharmacists	Time spent	Salary payments
Training of 'referents' (physicians indicated by each PGC)	Time spent	Salary payments
Printed materials	Invoices	Invoices
Travels costs	Estimate of distance to practices	Travel invoices
Cost of pharmacists doing outreach and making appointments	Record of number of visits and days spent on visits	Salary payments
Cost of other administrative tasks	Estimated time expenditure	Salary payments
Cost of physician time	Record of length of outreach visit and number of physicians	Salary payments
Development of software	Invoices, estimates of time spent	Invoices, salary payments
Drug expenditure	Medical records of prescribing	Italian Agency for Drug 2006

We will perform a sensitivity analysis, considering how variations of different parameters can affect results. Specifically, on the cost side we will consider different values in both quantities and prices of the consumed resources. On the effectiveness side, we will consider the boundaries of the confidence intervals. Moreover, we will perform best case/worst case analysis considering incremental values for cost and effectiveness (lower costs and better effectiveness vs higher costs and lower effectiveness).

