#### Secondary outcomes

• difference in the % of patients who were prescribed the specific drug(s)

• difference in the % of patients who were prescribed the specific drug(s) for the first time (in the previous 12 months)

• difference in expenditure for the specific drug (per 1000 patients/day)

• difference in NHS prescription of drugs under scrutiny (expressed as DDD per thousand inhabitants/day), comparing those who have received the "traditional" vs "enriched" format, and any information vs no information (Sardinia study only)

• differences in the main and secondary outcomes in each of the regions involved (cluster study only);

• differences in the main and secondary outcomes according to the n. of assisted population in the related PCG (cluster study only)

• differences in the main and secondary outcomes according to the terziles of physicians age

• adjusted difference in prescribed DDD per 1000 patients/day according to a statistical model, considering as possible covariates: overall prescription in DDD per 1000 patients day at baseline; n. of physicians in the specific PCGs; n. of assisted population; region (Emilia-Romagna or Friuli Venezia Giulia); geographical location (mountain, hill, plain, urban centre – according to definitions given by the Italian Statistics Institute); age distribution of assisted population (in quartiles); % females in the assisted population; physician age; total physician drug expenditure (excluding drugs under scrutiny); % assisted population with polyprescription (≥ three drugs of different classes); n. new prescriptions (in the last 12 months); month of evaluation; participation to the information meetings; % exact answers to the questionnaire testing knowledge (see additional file 1);

• difference in the variability (expressed as standard deviations) of prescription of drugs under scrutiny within PCGs (cluster study only)

• difference in knowledge (measured through the n. of correct answers to a specific anonymous questionnaire, see additional file)

• difference in attitudes (measured through the answers to a specific questionnaire, see additional file)

Drugs whose NHS prescription will be considered for the first two topic chosen are specified here below:

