1. for benign prostatic hyperplasia, the main indicators will be: difference in the prescription of 5 alpha-reductase inhibitors (finasteride and dutasteride, for which a reduction is expected); and difference in the ratio between the prescription of alpha blockers terazosin plus tamsulosin (already off patent drugs) versus other drugs of the same classes available in Italy (alfuzosin plus doxazosin – an increase of this ratio is expected). Secondary indicators will be: difference in the prescription of each of the alpha blockers listed above (a reduction is expected); difference of concomitant prescription of 5 alpha-reductase inhibitors and alpha blockers; and overall difference in expenditure for either 5 alpha-reductase inhibitors or alpha blockers (a reduction is expected for both of these indicators).

2. for the primary prevention of osteoporotic fractures, the main indicators will be: difference in the prescription of either alendronic acid or of sodium risedronate (a reduced increase is expected for both of these indicators, especially for the latter – for which the generic form is still unavailable). Secondary indicators will be: difference in the prescription of raloxifene and strontium ranelate (a reduction is expected for both of these indicators); and difference in the ratio between the prescription of alendronic acid (already off patent) versus the other two oral bisphosphonates available in Italy (sodium risedronate and ibandronic acid – an increase of this ratio is expected)

Physicians' expectations, perceived barriers and the added value about the proposed intervention will be eventually evaluated through focus groups with a sample of participating doctors for each region (at the end of the spring and the autumn rounds).

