### Sample size estimates

#### Emilia-Romagna and Friuli Venezia Giulia study (cluster RCT)

From a sample of 40 clusters (about 600 physicians) and using a dedicated software (Cluster Randomisation Sample Size Calculator version 1.0.2, Health Services Research Unit, Aberdeen University) we estimated the intracluster correlation coefficients (ICC) and the sample size that would be required to see a difference of 10% in the prescription of a number of possible drugs (15% for bisphosphonates), assuming an average cluster (PCG) size of 15 (Table 2).

**Table 2 T2:** Estimates of sample sizes to detect a prescribing difference of 10% (with two-tailed test)

	ATC code	Estimate of ICC	Sample size (NCP)
macrolides	J01FA	0.024	68
fluoroquinolones	J01MA	0.030	68
antidepressants	n06ab	0.058	88
nitroderivatives	C01da02, 05,08,14	0.09	96
bifosphosphonates **(15% diff)**	M05ba	0.062	106
proton pump inhibitors	A02BC	0.087	108
phosphomicine	J01xx01	0.014	108
Alfa blockers (for IPB)	g04ca + g04bx49	0.075	116
doxazosin (for IPB)	c02ca04	0.038	128
long acting β2 broncodilators + corticosteroids	R03AK06 e R03AK07	0.092	148
Finasteride +dutasteride	g04cb	0.08	154
opioids	N02A	0.061	164
clarithromicine	J01fa09	0.02	172
esomeprazole	A02bc05	0.023	204
long acting β2 broncodilators	R03AC12 e R03AC13	0.033	208
alendronate	M05ba04	0.08	218
finasteride	g04cb01	0.1	220
salmeterol + corticosteroids	R03ak06	0.102	234
bifosphosphonates	M05ba	0.062	238
azitromicine	J01fa10	0.068	266
risedronate	M05ba07	0	374
norfloxacine	J01ma06	0.055	386
fentanyl	N02ab03	0.043	428
salmeterol	R03ac12	0.053	698
morphine	N02aa01	0.05	2224
buprenorphine	N02ae01	0	Nc
bicalutamide	l02bb03	0	Nc
escitalopram	N06ab10	0	1434
levocetirizine	R06ae09	0.032	>600
antiandrogens	L02bb01+ L02bb03	0	nc

Since we expect to recruit about 150 PCGs we choose for the first round of information meetings the two topics previously described ('drugs for the treatment of benign prostatic hyperplasia', and 'drugs for the primary prevention of osteoporotic fractures in elderly people') because of the clinical relevance of the information to be presented.

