## Discussion

The two proposed RCTs will let us better understand the potential usefulness of NHS pharmacists assuming a more active role in transferring evidence-based information to physicians. Besides data on prescribing impact, the studies will provide qualitative insight on the feasibility of such information programs, with special attention to how different organizational settings in different regional areas may lead to better or worse implementation. As already said, these studies represent an unprecedented effort to accomplish such evaluations on quite a large scale and in a 'natural' organizational setting, which would be minimally altered by the interventions themselves. Moreover, the two RCTs will test two different strategies of information delivery: using small groups or one to one meetings. While these strategies will not be directly compared (being not employed in the same study but in two different ones), their feasibility and impact will be critically evaluated, also in light of other experiences described in the scientific literature and of methods used by the pharmaceutical industry to bring information to doctors on a large scale.

Last but not the least, the role of the format of medical information will be investigated: this could be a critical part in the implementation of information programs and its importance may be often underestimated, considering that medical schools generally do not offer the necessary tools to unscramble data published in the scientific literature; that average doctors do not have enough time to select and read what may add relevant information to their knowledge; and that, eventually, the uptake of this information may be facilitated by offering it in a clear, direct and appealing fashion, looking at the context of clinical practice [17].

As usually happens, the evaluation of complex interventions is intricate given the many different variables into play: it is the other side of the pragmatic nature of these RCTs, which is also, and undoubtedly, one of their strengths. Moreover, the ambitious quantitative hypothesis to be tested (10 or 15% difference in doctors' prescriptions) will not be easily demonstrated, in spite of the involvement of about 2000 physicians in the cluster RCT and about 900 in the single doctors RCT: an even larger sample size would have been necessary to see smaller but still relevant prescribing differences.

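### The comparison of drug savings with intervention cost is promised only if meetings prove more effective, a criterion left undefined; this biases its central estimate upward in expectation and promises no net cost otherwise

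*Protocol article*

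**What the plan says.** In the protocol article, Economic analysis opens with a condition: if meetings "will be more effective than no meetings, we will conduct economic evaluations for each study". The evaluation is then described: "we will conduct a cost-minimisation analysis evaluating whether the savings on drug-costs are greater than the costs of the intervention". No test, threshold, topic or indicator is attached to the condition.

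Two other parts of the plan bear on it.

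- **Expenditure outcomes.** The section Secondary outcomes lists, without any condition, the "difference in expenditure for the specific drug (per 1000 patients/day"). For the prostatic hyperplasia topic it also lists the "overall difference in expenditure for either 5 alpha-reductase inhibitors or alpha blockers".
- **Sensitivity analysis.** The end of Economic analysis states: "On the effectiveness side, we will consider the boundaries of the confidence intervals". It adds a best case and a worst case, the latter pairing higher costs with lower effectiveness.

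The Discussion says that the hypothesised 10 or 15% difference "will not be easily demonstrated, in spite of the involvement of about 2000 physicians in the cluster RCT", and that smaller but still relevant differences would have needed a larger sample.

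**The concern.** The effect estimate that decides whether the evaluation is run also drives the savings side of it. When an estimate is used only if it looks favourable, its average over the occasions on which it is used exceeds the truth. A base case built on it leans towards finding that the programme pays for itself.

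The rule is also silent where an answer would be most useful. An effect that is real but not demonstrated does not mean zero savings. Training, bulletins and visits will have been paid for, yet nothing in the document says that net cost will be reported in that event. The article says the intervention might later be offered routinely in the Italian health service, and the net cost bears directly on that decision.

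Because the criterion is undefined, it could also be settled after the data are seen. The cluster trial has four topic comparisons, and each first-round topic has more than one main indicator.

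**Working it through.** **Inputs from the article**

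- About 150 Primary Care Groups (PCGs) expected (Sample size estimates).
- PCGs required, from Table 2, headed "Estimates of sample sizes to detect a prescribing difference of 10% (with two-tailed test": alpha blockers 116, finasteride plus dutasteride 154, alendronate 218, risedronate 374, bisphosphonates 238 at 10% and 106 at 15%.
- Finasteride plus dutasteride, alendronate and risedronate are main indicators. The alpha-blocker and bisphosphonate rows are drug classes belonging to the two chosen topics.

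**Assumptions, not in the article**

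- Two-sided alpha 0.05.
- Design power 0.80, with 0.90 as the other end of the range.
- Table 2 counts are totals over both arms.
- Money saved is proportional to the prescribing effect.
- The condition is applied to the same estimate that is then costed.

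**Check on Table 2.** Required size scales with 1/(difference)². From the 10% row for bisphosphonates, 238 × (10/15)² = 105.8, which rounds up to the listed 106. The absolute counts cannot be rebuilt, because standard deviations, means, alpha and power are not given. The economic section itself contains no figure to reproduce.

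**Formula.** Let f be the true effect as a share of the design effect, and let

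θ = (1.960 + z_power) × √(150/N) × f

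be the true effect in standard errors. If the evaluation runs only when the estimate exceeds c standard errors in the favourable direction,

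E[estimate | run] / truth = 1 + φ(c − θ) / (θ Φ(θ − c)),

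with c = 1.96 for a significance rule and c = 0 for a favourable point estimate.

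**Example: finasteride plus dutasteride, N = 154, power 0.80**

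- f = 1: θ = 2.802 × √(150/154) = 2.765. Chance of passing Φ(0.805) = 0.790. Ratio 1 + 0.2885/(2.765 × 0.790) = 1.13.
- f = 0.5: θ = 1.382. Chance of passing 0.282. Ratio 1 + 0.3377/(1.382 × 0.282) = 1.87.
- f = 0.5, point-estimate rule: 1 + 0.1534/(1.382 × 0.917) = 1.12.

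**All rows, design power 0.80**

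| Row (N) | Significance, f = 1 | Significance, f = 0.5 | Point estimate, f = 1 | Point estimate, f = 0.5 |
|---|---|---|---|---|
| Bisphosphonates, 15% (106) | 1.05 | 1.60 | 1.00 | 1.06 |
| Alpha blockers (116) | 1.07 | 1.66 | 1.00 | 1.07 |
| Finasteride + dutasteride (154) | 1.13 | 1.87 | 1.00 | 1.12 |
| Alendronate (218) | 1.25 | 2.18 | 1.01 | 1.20 |
| Risedronate (374) | 1.52 | 2.79 | 1.05 | 1.37 |

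With design power 0.90, the significance columns become 1.02–1.36 at f = 1 and 1.42–2.43 at f = 0.5.

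The alendronate and risedronate rows use the 10% difference of Table 2. If the 15% difference was meant for them too, the counts become 218 × (10/15)² = 96.9 and 374 × (10/15)² = 166.2. The significance ratios at f = 1 then fall to 1.04 and 1.15.

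**Lower confidence limit after selection on significance.** Its mean as a share of the truth is the ratio minus 1.96/θ. For finasteride plus dutasteride this is 1.13 − 1.96/2.765 = 0.42 at f = 1 and 1.87 − 1.96/1.382 = 0.45 at f = 0.5. For alendronate it is 0.41 and 0.49. Coverage of the 95% interval given a significant result, at f = 0.5, is about 91% and 88% respectively.

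**Without the condition** there is no selection, and the expected ratio is 1.00.

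**The case against.** The best defence is that the plan already limits the damage. Several stronger readings are tempting, and the article does not support them.

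- **That all reported savings are selected.** They are not. Expenditure differences are unconditional secondary outcomes; only their comparison with intervention cost is conditional.
- **That the sensitivity analysis is worthless because both limits show a saving once significance is required.** No significance rule is stated. The comparison is with the cost of the programme, not with zero, so a positive lower limit can still mean a net loss. Even after selection on significance, the lower limit averages only about 0.4–0.5 of the true effect in the two rows checked, and a worst case is planned as well. This defence stands for the lower end. It does not reach the base case, and these analyses run only once the condition has been met.
- **That topics without an effect drop out of the costing.** The condition is worded for each study, and Table 1 of the article lists training, materials and outreach with no exclusion by topic. A study-level condition over several topics would not behave exactly as the single-estimate formula does.
- **That an overstatement of nearly twofold is to be expected.** That needs a significance rule together with a true effect of about half the design value. The Discussion says only that the effect will be hard to demonstrate, not that a small effect is likely.
- **That the same figures apply to Sardinia.** The article says its roughly 900 physicians exceed the number needed, which points to smaller inflation there.

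It may also be said that a condensed article can leave the criterion to a fuller document. That is fair for the definition of more effective. It does not answer the condition itself, which the article states as a rule.

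**Conclusion.** The point holds in limited form. Net cost is promised only after a favourable effectiveness result from the same data, under an undefined criterion. The central estimate of the net comparison is then biased upward in expectation; it is not certain to overstate in the trial at hand. Nor is any net cost promised when the effect is modest or imprecise, a possibility the Discussion allows for.

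Under the assumptions listed, with design power 0.80, the expected ratio of estimated to true effect runs from about 1.0 to 2.8. It is close to 1 for well-powered drug groups at the design effect, or if a favourable point estimate is all that is required. It is large only if significance is required and the true effect falls well short of the design effect. The link from prescribing effect to money is itself an assumption: one main indicator for prostatic hyperplasia is a ratio between alpha blockers, for which proportional savings are not established.

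The change is worth making because it removes the selection outright at almost no cost.

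**What to change.** Delete the opening condition in Economic analysis. State that the cost comparison will be run and reported for both studies whatever the prescribing result. Use the intention-to-treat difference with its full confidence interval, and charge the full intervention costs of all topics delivered. Keep the planned confidence-limit and worst-case analyses alongside.

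If the condition has to stay, the least that is needed is to define more effective in advance (indicator, topic and criterion) and to report intervention costs in every case. That would leave the base case selected.

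The cost is one sentence of protocol text and a little more analysis. The Table 1 inputs are mainly time records, invoices, visit records and prescribing data.

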### Follow-up

The follow-up time will be six months after each intervention. A further evaluation will be carried out after 12 months to assess persistence

### Information retrieval

Monthly prescription data will be retrieved from provincial drug prescription databases. Although impossible to eliminate completely, information bias due to database accuracy should not affect our evaluation significantly, since limited error rates are expected.

In the cluster RCT, knowledge and attitudes of physicians will be evaluated through separate questionnaires distributed during the information meetings. Each set of questions will be topic dependent, therefore questionnaires will be developed for each topic. The additional file shows the questionnaires related to the first two topics.

The knowledge questionnaire will be 'nominal' and filling up it will be necessary for receiving CME credits, while the attitude questionnaire will be anonymous so that responders can express their views freely.

### Monitoring of the study

After each meeting, pharmacists will report basic information (n. of participating physicians, duration, critical questions, active participation of 'referents', active participation to discussion, n. returned questionnaires, etc) on an online database. The coordinating centre (CeVEAS) will check that meetings are carried out according to randomisation by monitoring the database, showing up to about 10% of the meetings at random (for the cluster study) and contacting physicians by phone (for the Sardinia study)

### Sample size estimates

#### Emilia-Romagna and Friuli Venezia Giulia study (cluster RCT)

From a sample of 40 clusters (about 600 physicians) and using a dedicated software (Cluster Randomisation Sample Size Calculator version 1.0.2, Health Services Research Unit, Aberdeen University) we estimated the intracluster correlation coefficients (ICC) and the sample size that would be required to see a difference of 10% in the prescription of a number of possible drugs (15% for bisphosphonates), assuming an average cluster (PCG) size of 15 (Table 2).

**Table 2 T2:** Estimates of sample sizes to detect a prescribing difference of 10% (with two-tailed test)

	ATC code	Estimate of ICC	Sample size (NCP)
macrolides	J01FA	0.024	68
fluoroquinolones	J01MA	0.030	68
antidepressants	n06ab	0.058	88
nitroderivatives	C01da02, 05,08,14	0.09	96
bifosphosphonates **(15% diff)**	M05ba	0.062	106
proton pump inhibitors	A02BC	0.087	108
phosphomicine	J01xx01	0.014	108
Alfa blockers (for IPB)	g04ca + g04bx49	0.075	116
doxazosin (for IPB)	c02ca04	0.038	128
long acting β2 broncodilators + corticosteroids	R03AK06 e R03AK07	0.092	148
Finasteride +dutasteride	g04cb	0.08	154
opioids	N02A	0.061	164
clarithromicine	J01fa09	0.02	172
esomeprazole	A02bc05	0.023	204
long acting β2 broncodilators	R03AC12 e R03AC13	0.033	208
alendronate	M05ba04	0.08	218
finasteride	g04cb01	0.1	220
salmeterol + corticosteroids	R03ak06	0.102	234
bifosphosphonates	M05ba	0.062	238
azitromicine	J01fa10	0.068	266
risedronate	M05ba07	0	374
norfloxacine	J01ma06	0.055	386
fentanyl	N02ab03	0.043	428
salmeterol	R03ac12	0.053	698
morphine	N02aa01	0.05	2224
buprenorphine	N02ae01	0	Nc
bicalutamide	l02bb03	0	Nc
escitalopram	N06ab10	0	1434
levocetirizine	R06ae09	0.032	>600
antiandrogens	L02bb01+ L02bb03	0	nc

Since we expect to recruit about 150 PCGs we choose for the first round of information meetings the two topics previously described ('drugs for the treatment of benign prostatic hyperplasia', and 'drugs for the primary prevention of osteoporotic fractures in elderly people') because of the clinical relevance of the information to be presented.

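### About 150 PCGs do not reach a 10% difference for either osteoporosis main indicator and narrowly miss 15% for risedronate; the one osteoporosis row of Table 2 that fits sizes a different outcome

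*Protocol article*

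**What the plan says.** All references are to the protocol article, cluster RCT.

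- **Indicators.** Item 2 of the drug list under Secondary outcomes says of osteoporosis that "the main indicators will be: difference in the prescription of either alendronic acid or of sodium risedronate". It then states what is expected for both, so these are two outcomes, not one. The bisphosphonate class total appears neither as a main nor as a secondary indicator.
- **Target.** Sample size estimates gives the sizing aim as "to see a difference of 10% in the prescription of a number of possible drugs (15% for bisphosphonates"). The calculation takes 15 GPs as the mean for each PCG. Table 2 is titled "Estimates of sample sizes to detect a prescribing difference of 10% (with two-tailed test"). Its only row marked for 15% is the bisphosphonate class.
- **Osteoporosis rows of Table 2.** Alendronate: ICC 0.08, 218 PCGs. Risedronate: ICC 0, 374 PCGs. Class M05BA: ICC 0.062, 238 PCGs at 10% and 106 at 15%.
- **Expected sample.** The section continues: "Since we expect to recruit about 150 PCGs we choose for the first round of information meetings the two topics previously described", and gives clinical relevance as the reason. The Abstract equates about 150 PCGs with about 2000 GPs.
- **Claim.** The Discussion refers to "the ambitious quantitative hypothesis to be tested (10 or 15% difference in doctors' prescriptions"). It calls this hard to demonstrate and adds that a still larger sample would have been needed for smaller differences.

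**The concern.** The outcome that was sized and the outcomes that were named are not the same. For osteoporosis, the one row that 150 PCGs can satisfy belongs to a class total that the trial does not list. The rows for the two listed drugs exceed the expected number by 45% (218/150 = 1.45) and 149% (374/150 = 2.49). No 15% figure is printed for either drug, so a reader cannot tell from the article what the design can detect on its own main indicators.

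The Discussion makes this worse by implying that 10 or 15% is covered. The larger shortfall is on risedronate, the drug for which the article expects the clearer effect. A non-significant result there could be given more weight than the design supports.

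**Working it through.** **Inputs.** Required PCGs, ICCs and the cluster size of 15 come from Sample size estimates and Table 2. The expected 150 PCGs and 2000 GPs come from the Abstract. Alpha, power, and the mean and SD of prescribing are not stated, so 218 and 374 cannot be rebuilt from first principles. I read the Table 2 column as PCGs over both arms together, because every exact figure in it is even.

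**1. Check the table's scaling.** With all else fixed, the required number varies as 1/d². For the class, 238 × (10/15)² = 238/2.25 = 105.8, printed as 106. The table follows the rule, so it can be applied to the single drugs.

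**2. PCGs needed at 15%.**
- Alendronate: 218/2.25 = 96.9, about 97, inside 150.
- Risedronate: 374/2.25 = 166.2, about 167, outside 150.

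**3. Detectable difference at 150 PCGs of 15 GPs**, d = 10% × √(N/150). This holds the table's own power and needs no assumption about what that power was.
- Alendronate: 10% × √(218/150) = 12.1%.
- Risedronate: 10% × √(374/150) = 15.8%.

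**4. Smaller clusters.** 2000/150 = 13.3 GPs per PCG, not 15. N is rescaled by [(1 + (m − 1)ICC)/m] at m = 13.33, divided by the same term at m = 15.
- Alendronate: (1.987/13.33)/(2.12/15) = 1.054; N = 229.8 at 10% and 102.1 at 15%; d = 12.4%.
- Risedronate: 15/13.33 = 1.125; N = 420.8 at 10% and 187.0 at 15%; d = 16.75% (16.8% if N is first rounded up to 421).

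**5. Power at 150 PCGs**, under an assumed two-sided alpha of 0.05 and an assumed planning power of 80% (90% in brackets): Φ[(d/10%)(1.96 + z_power)√(150/N) − 1.96]. For example, risedronate at 10% under 80% planning is Φ(2.80 × 0.633 − 1.96) = Φ(−0.19) = 43%.

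| Indicator | GPs per PCG | Power at 10% | Power at 15% |
|---|---|---|---|
| Alendronate | 15 | 64% (77%) | 94% (98%) |
| Alendronate | 13.3 | 62% (75%) | 92% (98%) |
| Risedronate | 15 | 43% (54%) | 76% (87%) |
| Risedronate | 13.3 | 39% (49%) | 71% (83%) |

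**The case against.** The strongest reply is that 15% was the intended target for this topic, that the text can be read as applying it to bisphosphonates generally, and that 218 and 374 are 10% figures. On that reading alendronate is comfortably covered, and risedronate falls short by a detectable difference of 15.8% instead of 15%, against an expected number that is itself approximate. This stands, and it limits the point. It does not remove it: Table 2 marks only the class row for 15%, risedronate still misses, and the gap widens with 13.3 GPs per PCG.

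The second reply is disclosure. Table 2 prints both unfavourable rows, the topic was chosen for clinical relevance and not on a claim of power for each drug, and the article calls its target ambitious. That is fair, but incomplete: the Discussion attributes the need for a larger sample only to smaller differences, and Table 2 contradicts this for both drugs at 10%.

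Covariate adjustment might add precision. The Statistical analysis section ties ANCOVA for the primary outcomes to baseline imbalance, though, and the sizing claims no such gain.

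Two stronger readings are tempting and should be resisted:
- A reader might infer that neither 10% nor 15% is delivered for osteoporosis. The table's own scaling shows that 15% is delivered for alendronate.
- A reader might infer that the prostate topic is unsized as well. Its 5-alpha-reductase row needs 154 PCGs against about 150, which is met for practical purposes (10% × √(154/150) = 10.1%). The article never claims to have sized the alpha-blocker ratio, and a missing row for it is detail that an article may leave to the full protocol.

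**Conclusion.** The point holds in a limited form. About 150 PCGs do not reach 10% for either osteoporosis main indicator. They reach 15% for alendronate and narrowly miss it for risedronate. The only osteoporosis row that fits the expected sample sizes an outcome that is not listed, and the Discussion's implied sensitivity is too favourable for the two that are.

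The scaling and the detectable differences at 15 GPs per PCG rest on Table 2 alone, given that its figures are totals over both arms. If they are per arm, the detectable differences rise by a factor of √2, and alendronate would no longer reach 15% (about 2 × 97 = 194 PCGs). The power figures rest further on the assumed alpha and planning power. The risedronate ICC of 0 is an estimate from 40 clusters, and a positive value would raise its required number.

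Severity: should-fix. Table 2 is arithmetically consistent on the one check available. The fault lies in the match between sized and named outcomes, and in the claim built on it.

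**What to change.** In Sample size estimates and in the Discussion:

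- State the detectable difference at about 150 PCGs for each osteoporosis main indicator, at Table 2's power: about 12.1% for alendronate and 15.8% for risedronate with 15 GPs per PCG, or about 12.4% and 16.7% with 13.3. State the power and alpha that the table used.
- Say that the class row (15%, 106 PCGs) does not size these two indicators.
- Say that a non-significant result on risedronate does not by itself exclude a 15% difference, and that the confidence interval has to be read.
- Amend the Discussion sentence that reserves the need for a larger sample to smaller differences.

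The cost is a few sentences and a less favourable stated sensitivity for this topic. No extra PCGs are needed and the main indicators can stay as they are. Replacing them with the class total would be a debatable trade-off, because a total cannot show the drug-specific effect that the article expects for risedronate.
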